### Ethical and regulatory considerations

The trial has received approval from an NHS Research Ethics Committee (NHS REC, 16/WM/0134) for approval. Site-specific approvals for NHS PIC sites have been obtained. This is consistent with the requirements of OBU, who has agreed to act as the trial sponsor. All protocol and trial amendments (both minor and major) will be submitted through the ethics committee and, once approved, will be communicated to the sponsor and funding body and to the steering committee. The confidentiality of participants will be preserved in accordance with the Data Protection Act 1998. All participants will be allocated a unique identifier, and all trial data collected will be held in a linked anonymised form. Identifiable information will be stored separately from trial data. The randomisation will be held by a member of the research team who will oversee the trial but will not be involved in data collection or analysis. Group allocation will be referred by this same member and will ensure double blinding.

### Dissemination policy

Results of this trial will be reported in the first instance to the funders and then communicated to participants and relevant health professionals in a series of open access publications within 9 months of the end of the data collection. Authorship will follow the trial publication policy that has been developed based on *British Medical Journal* rules on authorship and contributorship. All publications will be deposited in the university open access forum for publications and, as much as possible, will be published in open access journals and will be open access on demand. The *BMJ* guidelines on writing authorship will be adhered to, and all members on the trial steering committee will sign and agree.

### Discontinuing

Participants will be advised to discontinue the trial if they find consuming the cocoa unacceptable or if consuming the cocoa is associated with in any related or unrelated AEs. Discontinuation of the trial will ultimately be decided by the PI and consultant medic.

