### Retention

We will make every effort to reduce loss to follow-up. One primary contact within each centre will contact all participants and act as liaison with the blinded assessor. The primary contact person will obtain information about the participants’ preferred method of contact (text, telephone, email and letter) and contact them using this preferred method when possible. They will also ask the participant for details of a nominated person who can be contacted if the team is unable to make contact with them, and we will retain details of the participant’s general practitioner. Contact details will be updated if applicable at each assessment. All appointments will be made at the research participant’s convenience wherever possible. If an appointment is missed we will try to rearrange this on two more occasions.

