### Data management

All work undertaken as part of this trial will comply with the Research Governance Framework for Health and Social Care UK and the OBU Research Governance Framework. All participant identification and referral procedures as well as procedures for data storage, processing and management will comply with the Data Protection Act 1998. All assessment data will be collected face-to-face using paper data collection forms. AE forms will be collected in person by one of the research team at OBU named in the delegation log. The retention period complies with guidelines set out by the OBU Research Governance Framework. Any individual who discontinues or deviates from the intervention will still have their data included in the data analysis.

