### Statistical methods

We will report summary statistics for demographics and outcome data of the study participants. The assessment of mediators is important to be able to identify the processes by which the intervention may bring about change. The proportion of adherence to the intervention will be reported descriptively with 95% confidence intervals. Graphical illustration will be used to check distributions of outcome data. As an exploratory trial, the primary outcome measures will be feasibility and acceptability. Results will be presented using point estimates, 95% confidence intervals and *p* values. The primary statistical analysis will be on an intention-to-treat basis, and the primary analysis will use the complete case data set. Exploratory analyses will be used to investigate the impact of individual demographic factors as well as theoretical mediators (i.e. disease/fatigue severity) on the intervention effect using appropriate correlation coefficients.

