#### Acceptability

The acceptability of the intervention will be measured through the end-of-study interview, which uses questions to measure the extent to which participants found the intervention and materials useful, enjoyable and beneficial.

Exploratory analyses will be used to investigate the impact of individual demographic factors as well as theoretical mediators on the short-term benefit of the intervention, using appropriate correlation coefficients.

A generalised linear model analysis will investigate whether fatigue differed between the treatment arms. This will be extended to joint modelling of both fatigue and physical functioning if there is a significant difference in the reported fatigue. Data may be transformed to improve model fit, or different regression approaches used (e.g. negative binomial or Poisson regression).

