### Feasibility

We will consider the acceptability of the intervention to participants, the ability of centres to recruit participants, the willingness of participants to be randomised, the number of eligible participants, the acceptability of the measures and the time taken to collect data.

From a design perspective, we have explicitly considered the burden with respect to timings of assessments and intervention sessions. AEs will be systematically documented, and if participants choose to discontinue the intervention, sites are encouraged to continue with outcome assessments wherever possible. Finally, data monitoring will be extensive to ensure minimisation of missing forms or data, and analysis will consider imputation methods as required. The data gathered here will inform the design (including sample size calculations) and delivery of a confirmatory phase III trial. In order to ensure repeatability in confirmatory trials, reporting will follow the template for intervention description and replication (TIDieR) reporting guidelines for description of interventions, and the Consolidated Standards of Reporting Trials (CONSORT) extension for non-pharmacological interventions. The possibility of refining measures will be considered by the research team, and key features of the feasibility trial will be considered for future work.

The end of the trial will be considered as the date on which the last participant has completed his or her final assessment.

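### People who find the drink unacceptable are advised to leave the trial, and so miss the completers-only interview that measures acceptability

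*Protocol article*

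**What the plan says.** All references are to the protocol article.

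- **Discontinuing.** "Participants will be advised to discontinue the trial if they find consuming the cocoa unacceptable". A second trigger follows: "if consuming the cocoa is associated with in any related or unrelated AEs". The decision is placed with the study leads: "Discontinuation of the trial will ultimately be decided by the PI and consultant medic".
- **Retention** (under Methods). "We will make every effort to reduce loss to follow-up".
- **Feasibility** (under Discussion). "if participants choose to discontinue the intervention, sites are encouraged to continue with outcome assessments wherever possible".
- **Data management.** "Any individual who discontinues or deviates from the intervention will still have their data included in the data analysis".
- **Statistical methods.** "the primary outcome measures will be feasibility and acceptability". The main analysis is described as intention-to-treat on complete cases.
- **Acceptability.** "The acceptability of the intervention will be measured through the end-of-study interview".
- **Process evaluation.** The interview takes place on exit at assessment 3 (week 6) and covers tolerance and acceptability of the drink. It is restricted to participants who complete the trial. The team will also try to reach those who drop out of the intervention and ask why they stopped.
- **Retention (i.e. assessments)** and **Adherence** (under Statistical methods). The first counts loss to follow-up. The second counts stopping the intervention. They are separate measures.

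**The concern.** Someone who dislikes the drink and stops taking it is covered by two instructions that conflict. Discontinuing advises that person to leave the trial. Feasibility, under Discussion, asks sites to keep assessing that person.

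The conflict bears on a primary outcome. Finding the cocoa unacceptable is a stated reason to be advised out of the trial, and leaving the trial removes the person from the interview that measures acceptability. The selection runs in one direction: those lost are the ones with an unfavourable view. Their views would also be useful if adherence fell in the range where the Adherence section would consider adjusting the intervention.

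Two further effects follow. Retention would partly reflect the protocol's own advice, and not only participants' willingness to be followed up. Complete-case fatigue estimates could also be affected, but only if leavers differ from stayers. The between-arm difference would be affected only if exit, or that gap, differs by arm.

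**Working it through.** The article states no figure to reproduce here, so the check has two parts.

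**1. The sections side by side**

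| Question | Discontinuing | Elsewhere |
|---|---|---|
| What does a person stop if the drink is unacceptable? | The trial | The intervention (Feasibility under Discussion; Data management; Adherence) |
| Are outcomes still collected afterwards? | Not if the person leaves as advised | Yes, where possible (Feasibility under Discussion) |
| Are stopping the drink and loss to follow-up distinct? | No, the second follows from the first | Yes, reported separately (Retention; Adherence) |
| Is the person interviewed on acceptability? | No, because interviews are for trial completers (Process evaluation) | Yes, if the person stays to assessment 3 |

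Data management keeps the data of people who discontinue the intervention. Data gathered before exit can still be used, but nothing new is collected from someone who has left.

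**2. Size of the selection**

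Inputs from the article: 40 randomised (Sample size); adherence thresholds of 75% and 65% (Adherence). The share of non-completers who leave the trial is not given, so it is assumed to range from none to all.

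- 75% of 40 = 30 and 65% of 40 = 26. Adherence above 65% and below 75% therefore means 27 to 29 people complete the cocoa.
- Non-completers: 40 − 29 = 11 to 40 − 27 = 13.

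With *d* non-completers and a fraction *f* of them leaving, their share of the interviewed group is *d*(1 − *f*) / (40 − *df*).

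| Fraction leaving | *d* = 11 | *d* = 13 |
|---|---|---|
| None | 11/40 = 27.5% | 13/40 = 32.5% |
| Half | 5.5/34.5 = 15.9% | 6.5/33.5 = 19.4% |
| All | 0/29 = 0% | 0/27 = 0% |

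For retention, each advised exit costs 1/40 = 2.5 percentage points.

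The article defines no proportion for acceptability, so no bias in such a proportion is computed. The size of any effect on fatigue cannot be derived from the article either.

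**The case against.** The best reply is that the word *trial* in Discontinuing is a slip for *intervention*. The rest of the article separates the two, and the Discussion gives the more specific instruction to continue assessments. On that reading, people who stop the drink reach week 6, count as completers and are interviewed, and most of the harm goes. This is plausible. It does not remove the literal rule that staff would follow, and anyone who does leave is still excluded by the completers-only limit.

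A second reply is that dropouts are contacted. The sentence after that promise lists topics that include barriers and suggestions for improvement, and these may apply to dropouts as well. This is a real mitigation. However, the contact is only attempted, and the Acceptability section names the interview, not this contact, as the measure.

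A third reply is that poor tolerance shows up elsewhere: in adherence, adverse events, duration of participation, unused cocoa and steering committee oversight. The 75% and 65% thresholds attach to adherence, where a person who stops counts against success whether interviewed or not. This stands. A favourable interview result could not by itself hide a badly tolerated drink. It could still misstate acceptability, which is a primary outcome in its own right.

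Finally, exit is advised and not automatic, and the principal investigator and consultant medic decide. That is ordinary protection for adverse events. It calls for stopping the drink and does not require ending follow-up, and the trigger as worded extends to unrelated events.

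**Conclusion.** The point holds. Discontinuing contradicts the Discussion's instruction to continue assessments. Combined with the completers-only interview, it would leave people who find the drink unacceptable under-represented, though not necessarily absent, in the measure of a primary outcome. The direction is towards a favourable result.

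In the article's own adjustment band, the non-completers' share of interviewees falls from 28% to 33% if all stay to 0% if all leave. This assumes that non-completion is due to unacceptability or adverse events. Other causes, such as missed sachets in people who remain in the trial, would shrink the effect, and the all-leave case is an extreme. The flaw does not endanger participants or invalidate the trial, but it should be corrected because the selection is avoidable and the remedy is cheap.

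**What to change.** - **Discontinuing:** state that participants stop the drink if they find it unacceptable, or if an adverse event is judged by the principal investigator and consultant medic to warrant it. They remain in the week 3 and week 6 assessments unless they withdraw consent. If this was always the intention, the change only makes it explicit.
- **Process evaluation:** replace the restriction to completers with an offer of the exit interview to everyone randomised who agrees.
- **Retention (i.e. assessments) and Adherence:** count as lost to follow-up only those who do not attend, and report separately those who stop the drink.

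The cost is mainly rewording in Discontinuing and Process evaluation, plus a few more visits and interviews with people who have stopped the drink. Stopping the drink for safety is unaffected.

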#### Auditing

The trial is open to auditing either through NHS governance or through the university’s Centre for Movement, Occupational and Rehabilitation Sciences governance committee.

### Statistical methods

We will report summary statistics for demographics and outcome data of the study participants. The assessment of mediators is important to be able to identify the processes by which the intervention may bring about change. The proportion of adherence to the intervention will be reported descriptively with 95% confidence intervals. Graphical illustration will be used to check distributions of outcome data. As an exploratory trial, the primary outcome measures will be feasibility and acceptability. Results will be presented using point estimates, 95% confidence intervals and *p* values. The primary statistical analysis will be on an intention-to-treat basis, and the primary analysis will use the complete case data set. Exploratory analyses will be used to investigate the impact of individual demographic factors as well as theoretical mediators (i.e. disease/fatigue severity) on the intervention effect using appropriate correlation coefficients.

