**Methods:**

Using a randomised (1:1) double-blind placebo-controlled feasibility study, 40 men and women (20 in each trial arm) with a recent diagnosis (< 10 years) of relapsing and remitting MS (RRMS) and who are over 18 years of age will be recruited from neurology clinics and throughout the Thames Valley community. During a 6-week nutrition intervention period, participants will consume the cocoa beverage, high flavonoid or low flavonoid content, at breakfast daily. At baseline, demographic factors and disease-related factors will be assessed. Fatigue, activity and quality of life, in addition to other measures, will be taken at three visits (baseline, week 3 and week 6) in a university setting by a researcher blinded to group membership. Feasibility and fidelity will be assessed through recruitment and retention, adherence and a quantitative process evaluation at the end of the trial.

We will describe demographic factors (age, gender, level of education) as well as disease-related factors (disease burden scores, length of time diagnosed with MS) and cognitive assessment, depression and quality of life and general physical activity in order to characterise participants and determine possible mediators to identify the processes by which the intervention may bring about change. Feasibility (recruitment, safety, feasibility of implementation of the intervention and evaluation, protocol adherence and data completion) and potential for benefit (estimates of effect size and variability) will be determined to inform future planned studies. Results will be presented using point estimates, 95% confidence intervals and *p* values. Primary statistical analysis will be on an intention-to-treat basis and will use the complete case data set.

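### The primary analysis is labelled intention-to-treat but limited to complete cases, so participants who leave follow-up drop out of the fatigue estimate meant to plan phase III

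*Protocol article*

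**What the plan says.** The Statistical methods section fixes the rule: "The primary statistical analysis will be on an intention-to-treat basis, and the primary analysis will use the complete case data set". The Methods paragraph of the abstract repeats it: "Primary statistical analysis will be on an intention-to-treat basis and will use the complete case data set".

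Three other statements bear on who ends up in that set:

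- **Data management:** "Any individual who discontinues or deviates from the intervention will still have their data included in the data analysis".
- **Discontinuing:** "Participants will be advised to discontinue the trial if they find consuming the cocoa unacceptable". The same advice covers adverse events, and the final decision rests with the principal investigator and the consultant medic.
- **Feasibility (in the Discussion):** "if participants choose to discontinue the intervention, sites are encouraged to continue with outcome assessments wherever possible". On missing data it adds that "analysis will consider imputation methods as required".

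The Feasibility part of the statistical methods accepts 80% completeness for each measure. The main outcomes are not efficacy outcomes: "the primary outcome measures will be feasibility and acceptability". The Acceptability section plans a generalised linear model comparing fatigue between arms. The Objectives say that effect size and variability, above all for fatigue, will inform a phase III trial.

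**The concern.** Intention-to-treat means that everyone randomised is analysed in the arm to which they were allocated. Complete case means that only those with the required outcomes are analysed. The two agree only when nothing is missing, and the plan itself expects missing outcomes. Used together as one primary rule, the second overrides the first.

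If people leave because they do not tolerate the drink, the complete cases are those who tolerated it. The fatigue difference and SD carried forward to phase III would then describe a selected group. The statement on imputation does not settle this: no method is named, and it is not tied to an analysis that both statements of the primary rule restrict to complete cases.

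**Working it through.** **Figure to reproduce.** There is none. The sample of 40 (20 per arm) rests on feasibility and recruitment, and the document gives no dropout rate, SD or target effect. The check is therefore on who is analysed, then on the possible size under stated assumptions.

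**Step 1: who is in which set.**

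| Participant | As randomised | Complete case |
|---|---|---|
| Takes the drink, attends all visits | in | in |
| Stops the drink, attends all visits | in | in |
| Attends week 3, then leaves | in | out if week 6 or all visits are required |
| Leaves before week 3 | in | out for any analysis that needs a post-baseline visit measure |

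The sets part in the last two rows. The third row is also where data already collected can be thrown away, which is what the Data management statement promises will not happen. Table 1 schedules Neuro-QOL at baseline, week 3 and week 6, so such a participant has a usable week 3 value.

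**Step 2: how many.** At the plan's own 80% mark, 0.80 × 40 = 32 remain on a measure and 8 are missing. If the loss is even, 16 per arm remain. The 95% confidence interval half-width for a difference in means, in SD units, is 1.96 × √(2/n):

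- n = 20 per arm: 1.96 × √(2/20) = 0.62
- n = 16 per arm: 1.96 × √(2/16) = 0.69

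**Step 3: bias in the arm difference.** Let p₁ and p₀ be the missing shares in the two arms. Let D be the gap in mean fatigue between leavers and completers, in SD units and equal in both arms. The complete-case difference is off by (p₁ − p₀) × D in absolute size. All values of p and D are assumptions.

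| Missing shares | D = 0.25 | D = 0.5 | D = 1.0 |
|---|---|---|---|
| 20% and 0% | 0.05 | 0.10 | 0.20 |
| 20% and 10% | 0.025 | 0.05 | 0.10 |
| 20% and 20% | 0 | 0 | 0 |

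The sign depends on which arm loses more people and on whether leavers are more or less fatigued. The document gives neither. The last row is zero only because D is taken as equal in both arms.

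**Step 4: bias in the SD.** Suppose a share p is lost from an arm, leavers and completers have the same spread, and D is in completer SDs. The full-arm SD is then √(1 + p(1 − p)D²) times the completer SD. With p = 0.20:

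- D = 0.25: √(1 + 0.16 × 0.0625) = 1.005
- D = 1.0: √(1 + 0.16 × 1) = 1.077

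The SD of completers would be too small by about 0.5% to 7% in that arm (1 − 1/1.005 and 1 − 1/1.077).

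**The case against.** The case for leaving the text alone has several parts.

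- **Stopping the drink is not the same as being excluded.** A reader might infer that complete case removes everyone who stops because of the drink. The document does not support that. Complete case removes people with missing outcomes, and someone who stops but attends the visits is kept and analysed as randomised. This stands.
- **The conflict with Data management is conditional.** That section promises inclusion of data, and data never collected cannot be included. The article also does not define a complete case by visit or by outcome, and the 80% mark is set per measure. It is therefore not certain that someone with week 3 but no week 6 would be discarded. This stands too. The rule as worded permits the loss but does not compel it.
- **The trial works to limit loss.** It offers home visits at week 3, tries twice more to rearrange a missed appointment, and asks for a nominated contact. It also plans to record intervention dropout and loss to follow-up. This may reduce the missing share but does not settle who is analysed.
- **The feasibility outcomes come first.** This stands and lowers the weight of the point. A reader might infer that the adherence and retention proportions are also computed among completers, because feasibility is primary and the primary analysis is complete case. The text does not support this: retention is the share lost to follow-up, which has no meaning among completers, and adherence is defined over the participants.
- **Even the largest assumed bias, 0.20 SD, is well inside a half-width of 0.62 to 0.69 SD.** This is true, and random error will dominate the estimate. It does not justify adding an avoidable selection to it.

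**Conclusion.** The point holds in limited form. The article calls its primary analysis intention-to-treat and restricts it to complete cases. Those sets differ once outcomes are missing, and the excluded participants are those who leave follow-up, which the Discontinuing section links to tolerance of the drink. Partial data they gave could be lost despite the Data management statement.

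The size cannot be fixed from the document. Under the assumptions above, the bias in the arm difference runs from zero (equal loss and equal gaps) to 0.05–0.20 SD (20% lost in one arm only, gap of 0.25–1.0 SD). A reader might infer that the bias favours cocoa. Nothing supports that: the drinks are designed to match in taste and appearance, and no arm-specific dropout is given.

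This should be fixed because the fatigue effect and SD are meant to plan phase III. It does not threaten the feasibility conclusions, and since the trial has no power target, the smaller set breaches none.

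**What to change.** 1. **In the abstract and in Statistical methods**, replace the complete-case rule for the fatigue comparison. State that participants are analysed in the arm to which they were randomised, using all available post-baseline data. One concrete form is a mixed model for repeated measures on Neuro-QOL at weeks 3 and 6, with arm by visit, baseline Neuro-QOL, gender and disease-modifying treatment. The last two are the stratification factors already in use.
2. **Move complete case to a sensitivity analysis**, and say which visits make a case complete.
3. **State the limits.** The model assumes data are missing at random. It does not recover people who leave before week 3, so report their number and reasons by arm. Say what role, if any, imputation has alongside it.
4. **Reconcile Data management, Discontinuing, Statistical methods and the Discussion's Feasibility section**, so that stopping the drink and leaving follow-up are treated as separate events throughout. Which clinical rule applies is for the trial team.

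Items 1 to 3 change analysis wording and need no new data. Item 4 may touch how follow-up is conducted, and could then need an amendment through the ethics committee.
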